## 2.2 Exploratory Endpoints

### 2.2.1 Definitions and Derivation of Exploratory Endpoints

Exploratory efficacy endpoints are defined as the difference between measurements (defined below) at baseline and at post treatment period (i.e. 0, 15, 30 and 40min):

- Plasma glucagon level is the concentration of plasma glucagon measured in pmol/L.
- Plasma somatostatin level is the concentration of plasma somatostatin measured in pmol/L.
- Blood glucose value is the concentration of blood glucose measured in mmol/L.
- Plasma C-peptide level is the concentration of plasma C-peptide measured in pmol/L.

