### **1.1.2 Exploratory Objectives**

1. To compare the plasma glucagon response during induced hypoglycaemia in people with T1D prior to glibenclamide treatment, and at each dose step, to that of participants without diabetes (non-DM group).
2. To compare the increase in plasma glucagon from euglycaemia to hypoglycaemia in T1D participants prior to treatment, and at each dose step of glibenclamide, to that of participants without diabetes (non-DM group).
3. To compare the percentage of time spent in hypoglycaemia (

**Table 1)** at each dose step of glibenclamide, compared to baseline (T1D group only)

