**Table 1 : Definition of hypoglycaemia**

|                |                                                                                                                       |
|----------------|-----------------------------------------------------------------------------------------------------------------------|
| Level 1 | < 4.0 mmol/L (70mg/dL) = glucose alert                                                                         |
| Level 2 | < 3.0 mmol/L (54mg/dL) = clinically important hypoglycaemia                                                    |
| Level 3 | <4.0 mmol/L with severe cognitive impairment requiring external assistance for recovery = severe hypoglycaemia |

4.To compare the change in plasma glucagon from euglycaemia to hypoglycaemia in T1D participants prior to and following administration of a single 10 mg dose of oral dapagliflozin, to that of participants without diabetes (non-DM group).

5.To compare the change in plasma somatostatin from euglycaemia to hypoglycaemia in T1D participants prior to and following administration of a single dose of dapagliflozin 10mg, to that of participants without diabetes (non-DM group).

6.To characterise the development of hypoglycaemic symptoms during induced hypoglycaemia at baseline, and during each dose of glibenclamide and dapagliflozin.

7.To measure any residual C-peptide participants with T1D only.

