## 5.4 Exploratory endpoint analyses

### 5.4.1 Analysis of exploratory endpoints

1. To compare the concentration of plasma glucagon measured in pmol/L during induced hypoglycaemia (at 0, 15, 30 and 40min) in people with T1D prior to glibenclamide treatment, and at each dose step (at 0.3mg, 0.6mg and 3mg), to that of participants without diabetes (non-DM group).

A mixed-effects model (treatment x time-point) will be used to compare plasma glucagon values at each time-point (0, 15, 30 and 40min) during the hypoglycaemic phase of the hyperinsulinaemic hypoglycaemic clamp at baseline (T1D and non-DM group) and at each dose step (T1D group only).

Post-hoc analysis will be performed which will allow pairwise comparisons between the plasma glucagon values obtained at each time-point (T1D and non-DM group, see **Table 3**).

2. To compare the proportion of change in plasma glucagon concentration from euglycaemia to hypoglycaemia at each time point (0, 15, 30 and 40min) in T1D participants prior to treatment, and at each dose step (at 0.3mg, 0.6mg and 3mg) of glibenclamide, to that of participants without diabetes (non-DM group).

We will calculate the proportion of increase in plasma glucagon at each time point by taking plasma glucagon values at each time-point (0, 15, 30 and 40min) during the hypoglycaemic phase of the hyperinsulinaemic hypoglycaemic clamp divided by the value at the corresponding time-point during the euglycaemic phase.

A mixed-effects model (treatment x time-point) will be used to compare the proportion increase in plasma glucagon as dependent variable (i.e. plasma glucagon concentration during the hypoglycaemic phase vs plasma glucagon concentration during the euglycaemic phase) at each time-point (0, 15, 30 and 40min) as independent variable at baseline (T1D and non-DM group) and at each dose step (T1D group only).

Post-hoc analysis will be performed which will allow pairwise comparisons between the plasma glucagon values obtained at each time-point (see **Table 3**).

3. To compare the percentage of time spent in hypoglycaemia

**Table 1** (<4.0mmol/L of blood glucose) at each dose step (at 0.3mg, 0.6mg and 3mg) of glibenclamide, compared to baseline (T1D group only). Three separate paired t-tests will be used to compare 0mg vs 0.3mg, 0mg vs 0.6mg and 0mg vs 3mg. If the assumptions of t-test are not satisfied, then the percentages will be treated as proportion and a 2 proportions test will be used.

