4. To compare the proportion of change in plasma glucagon levels measured in pmol/L at each time point 0, 15, 30 and 40min, (i.e. glucagon concentration at 0min during the hypoglycaemic phase divided by the glucagon concentration at 0min during the euglycaemic phase) from euglycaemia to hypoglycaemia in T1D participants prior to and following administration of a single 10 mg dose of oral dapagliflozin, to that of participants without diabetes (non-DM group).

Plasma glucagon values at each time-point (0, 15, 30 and 40min) during the hypoglycaemic phase of the hyperinsulinaemic hypoglycaemic clamp will be divided by the value at the corresponding time-point during the euglycaemic phase. A mixed-effects model (treatment x time-point) will be used to compare the proportion change in plasma glucagon (i.e. plasma glucagon during the hypoglycaemic phase vs plasma glucagon during the euglycaemic phase) after taking a single dose of dapagliflozin (T1D group only) versus baseline/no treatment (T1D and non-DM group).

Post-hoc analysis will be performed which will allow pairwise comparisons between the plasma glucagon values obtained at each time-point.

5. To compare the proportion of change in plasma somatostatin levels measured in pmol/L at each time point 0, 15, 30 and 40min (i.e. somatostatin concentration at 0min during the hypoglycaemic phase divided by the somatostatin concentration at 0min during the euglycaemic phase) from euglycaemia to hypoglycaemia in T1D participants prior to and following administration of a single dose of dapagliflozin 10mg, to that of participants without diabetes (non-DM group).

Plasma somatostatin values at each time-point (0, 15, 30 and 40min) during the hypoglycaemic phase of the hyperinsulinaemic hypoglycaemic clamp will be divided by the value of plasma somatostatin at the corresponding time-point during the euglycaemic phase.

A mixed-effects model (treatment x time-point) will be used to compare the proportion change in somatostatin (i.e. somatostatin during the hypoglycaemic phase vs. somatostatin during the euglycaemic phase) after taking a single dose of dapagliflozin (T1D group only) versus baseline/no treatment (T1D and non-DM group).

Post-hoc analysis will be performed which will allow pairwise comparisons using correlation [7] between the plasma somatostatin values obtained at each time-point.

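### SAP 5.4.1, items 2, 4 and 5: the mixed models use the hypoglycaemia/euglycaemia ratio, but the post-hoc pairwise comparisons are written for hormone levels

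*SAP*

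**What the plan says.** **Objectives (SAP 1.1.2).** Three exploratory objectives ask about a within-clamp response and name no scale:
- Objective 2: "To compare the increase in plasma glucagon from euglycaemia to hypoglycaemia in T1D participants prior to treatment", and at each glibenclamide dose, against the non-DM group.
- Objective 4: "To compare the change in plasma glucagon from euglycaemia to hypoglycaemia in T1D participants", before and after dapagliflozin.
- Objective 5: "To compare the change in plasma somatostatin from euglycaemia to hypoglycaemia in T1D participants", before and after dapagliflozin.

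**Endpoint definition (SAP 2.2.1).** "Exploratory efficacy endpoints are defined as the difference between measurements (defined below) at baseline and at post treatment period". The measurement for glucagon is the raw concentration: "Plasma glucagon level is the concentration of plasma glucagon measured in pmol/L". No quantity relating hypoglycaemia to euglycaemia is listed.

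**Analysis (SAP 5.4.1).** Item 2 derives a new variable: "We will calculate the proportion of increase in plasma glucagon at each time point by taking plasma glucagon values at each time-point" in the hypoglycaemic phase, "divided by the value at the corresponding time-point during the euglycaemic phase". Item 4 uses the same formula, and item 5 does the equivalent for somatostatin. That ratio is the outcome of the mixed model in all three items. The pairwise step in items 2 and 4 then reads: "Post-hoc analysis will be performed which will allow pairwise comparisons between the plasma glucagon values obtained at each time-point". Item 5 has a parallel sentence for the somatostatin values and adds that the comparison is made by correlation.

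**The concern.** The model and the pairwise step that follows it are written for different quantities. The ratio measures response to hypoglycaemia relative to that participant's own euglycaemic level in the same clamp. The raw value measures level. An analyst who follows the text literally would fit the model to one and report the pairwise results on the other.

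This matters because the pairwise results are what show which dose, or which group, differs from which. If they are on level, they can point to a treatment effect where the response has not changed, or miss a response that has. The risk is concrete for objective 4: SAP 1.2 says that dapagliflozin itself raises plasma glucagon within hours of dosing, so the euglycaemic value could shift as well as the hypoglycaemic one.

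There is a smaller point about the label. Item 2 calls hypoglycaemic over euglycaemic a proportion of increase, but that quotient equals 1 when nothing has changed.

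**Working it through.** The plan states no figure for this point, so there is none to reproduce. The check is a comparison of text, followed by an illustration. Write H for the hypoglycaemic value and E for the euglycaemic value at the same time-point.

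**1. Which quantity is used where**

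| Place | Quantity |
|---|---|
| Objectives 2, 4, 5 | increase or change from E to H, scale not stated |
| 2.2.1 | concentration, post-treatment versus baseline |
| 5.4.1 item 1, model and pairwise | H |
| 5.4.1 items 2 and 4, model | H/E |
| 5.4.1 items 2 and 4, pairwise | glucagon values, as worded in item 1 |
| 5.4.1 item 5, model | H/E (somatostatin) |
| 5.4.1 item 5, pairwise | somatostatin values, by correlation |

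Nothing elsewhere joins these up. Section 4.4 lists BMI as the only derived variable, and section 6.2 identifies no transformation.

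**2. Overlap of item 2 with item 1**

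The pairwise sentence is the same in both items, both refer to Table 3, and both use the same four time-points. Table 3 marks 4 + 3 + 2 + 1 = 10 pairs. Taken at each of four time-points, that is 10 × 4 = 40 comparisons. Read literally, item 2's 40 are item 1's 40 again. This does not carry over to item 4, because item 1 does not cover dapagliflozin.

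**3. Can level and ratio disagree?**

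Inputs: H = 5.54 pmol/L, the T1D hypoglycaemic mean quoted in section 1.3.4; E = 5 pmol/L, an assumption, since the SAP gives no euglycaemic value. The shifts of 30% are illustrative.

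Starting ratio: 5.54 / 5 = 1.108.

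| Change on treatment | Change in H | H/E after |
|---|---|---|
| A. E and H both rise 30% | 5.54 × 0.30 = +1.66 | 7.202 / 6.5 = 1.108 |
| B. Only H rises 30% | +1.66 | 7.202 / 5 = 1.440 |
| C. Only E falls 30% | 0 | 5.54 / 3.5 = 1.583 |

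A comparison of H cannot tell A from B, and it sees nothing in C. The conclusion does not depend on the assumed E: for any E, the ratio is multiplied by 1.3/1.3 = 1 in A, by 1.3 in B and by 1/0.7 = 1.43 in C.

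**4. The label**

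The fractional increase is (H − E)/E = H/E − 1. A 30% rise gives H/E = 1.30 and a fractional increase of 0.30. For two conditions, (H₁/E₁ − 1) − (H₂/E₂ − 1) = H₁/E₁ − H₂/E₂, so the constant 1 cancels from every contrast. Only the reported magnitude is affected.

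**The case against.** The strongest reply is that the pairwise sentence is loose drafting. It comes straight after a model whose outcome is the ratio, and pairwise comparisons after a model are ordinarily contrasts of that model's outcome. This may well be what was meant. The text does not say so, however, and the identical sentence in item 1 does refer to raw concentration. Either analysis could be run in good faith.

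Three further points stand and limit the finding:

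- **The objectives are still analysed.** The mixed models in items 2, 4 and 5 use the ratio and address the change from euglycaemia. A reader might infer that these objectives go unanswered; that holds only for the pairwise step read literally.
- **Section 2.2.1 is not a competing formula.** A reader might infer that its difference is H − E and that the plan therefore holds rival measures of the same response. The difference there runs between baseline and post-treatment. It can coexist with the ratio: derive H/E at each step, then compare with baseline. The defect in 2.2.1 is an omission.
- **No between-group size can be attached.** One might apply the same fold-rise to the two hypoglycaemic means in 1.3.4 (5.54 and 23.3 pmol/L) and infer that ratio and difference scales disagree about four-fold because the groups start from different levels. The SAP gives no starting (euglycaemic) level for either group, the two means come from different settings, and H − E is not a measure it proposes.

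On the label, the formula is written out, so the calculation itself is not in doubt.

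**Conclusion.** The point holds as a mismatch between model and pairwise step in 5.4.1. For items 2, 4 and 5 the pairwise comparisons, as written, are on hormone level and not on the change from euglycaemia to hypoglycaemia; for item 2 they duplicate item 1. In item 5, correlation adds a second problem: it measures association between values and does not test whether they differ.

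The finding rests on reading the pairwise sentences literally. How far level and ratio would diverge in the trial data cannot be stated without euglycaemic values; the illustration shows only that they can. The label error is exactly 1 on the fractional scale (100 percentage points) and leaves all contrasts unchanged.

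Only exploratory analyses are affected. The primary analysis in 5.3.1 uses the 40-minute concentration in the T1D group and is untouched. The correction is worth making because it is specific and nearly free, and because with no multiplicity adjustment (4.2) an ambiguous outcome leaves room to choose the scale after the results are seen.

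**What to change.** - **2.2.1:** add the hypoglycaemia/euglycaemia ratio, at each of 0, 15, 30 and 40 minutes, as the derived endpoint for objectives 2, 4 and 5, and list it in 4.4.
- **5.4.1 items 2, 4 and 5:** state that the pairwise comparisons are contrasts of that ratio, taken from the same mixed model. In item 5 these contrasts replace the correlation.
- **5.4.1 items 2, 4 and 5:** use one name for the ratio throughout, and report percentage change as 100 × (ratio − 1).

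The cost is a short SAP amendment, which the Introduction allows for, made before database lock. No new data, visits or assays are needed.

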### 2.2.2 Definitions and Derivation of Safety Endpoint(s)

Safety endpoint is defined as number of adverse events during treatment period of glibenclamide (at 0.3mg, 0.6mg or 3mg) and dapagliflozin **Table 4**.

### 2.2.3 Handling of Missing Data

All missing data will be handled as detailed in 2.1.4.

## 3 Analysis Sets/Populations

### 3.1 Protocol violations

A trial-related deviation is a departure from the ethically approved trial protocol or other trial document or process (e.g. consent process or IMP administration) or from Good Clinical Practice (GCP) or any applicable regulatory requirements. Any deviations from the protocol will be documented in a protocol deviation form and filed in the trial master file.

### **3.2 Intent-to-treat Population / Full analysis set**

The intention to treat population (ITT) is defined as the set of all randomised patients. Any patient found to have followed a sequence that is different from that to which they were randomised will be counted in the sequence to which they were randomised. Hence, data from all randomised participants will be included in the analysis.

### **3.3 Per-protocol Population**

The per-protocol population (PP) is defined as the set of all randomised patients that adhered to the protocol. There are no PP analyses.

### **3.4 Safety Population**

Safety population (SP) analysis is defined as the set of all randomised patients who were treated with glibenclamide and dapagliflozin.

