## 1 Introduction

Type 1 diabetes (T1D) affects around 400,000 people in the UK and is caused by nearly complete loss of insulin-producing cells in the pancreas. It is often challenging to achieve good control of blood glucose throughout the day in T1D, in part because of fluctuations associated with giving insulin. Severe episodes of low blood sugar levels, commonly called “hypos”, are one of the most feared complications of managing diabetes with insulin.

The impaired release of other hormones, such as plasma glucagon which raises blood sugar, during hypo episodes is also part of type 1 diabetes. A better understanding of this mechanism could lead to treatments aimed at reducing the risk of hypoglycaemia.

Glibenclamide is an oral anti-diabetic medication (sulfonylurea) which is commonly used to increase the amount of insulin released by the pancreatic beta-cells. Recent pre-clinical studies have shown that sulfonylureas can also improve plasma glucagon levels when used in very small doses by working on pancreatic alpha-cells, which release plasma glucagon. We have previously conducted a pilot study (LEGEND-A), which suggested that low doses of glibenclamide (0.3mg/day) could alter plasma glucagon release in some people with type 2 diabetes without increasing the risk of hypoglycaemia. In addition, another type of oral anti-diabetic medication, called dapagliflozin, has also been shown to work on pancreatic alpha-cells.

Therefore, the aim of this follow-up study (LEGEND-D) is to find out whether similar doses of glibenclamide or a single dose of dapagliflozin could increase plasma glucagon release in people with T1D. We hope that add-on therapies such as these may become a new way of helping people with T1D to prevent hypoglycaemia.

The trial will involve 2 groups of participants:

- a) 20 people with T1D, who will be given a liquid form of glibenclamide orally for a maximum of 54 days (at 3 different doses, in 3 blocks of 14-18 days), followed by a single oral dose of dapagliflozin, and undergo 5 controlled hypoglycaemia challenges.
- b) A control group of 10 people without diabetes, who will undergo one hypoglycaemia challenge without receiving any medication.

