## 1.2 Study Design

The LEGEND-D trial is a pilot, randomised cross-over, single-centre, non-blinded, clinical trial which aims to investigate the effect of 3 low doses of glibenclamide (0.3mg, 0.6mg and 3mg/day) assigned in all possible sequences followed by dapagliflozin (single dose of 10mg) on the plasma glucagon response during induced hypoglycaemia in people with type 1 diabetes, compared to non-diabetic individuals (**Figure 1**). The trial will be conducted by the Oxford Centre for Diabetes, Endocrinology and Metabolism (OCDEM) Clinical Research Unit (CRU) at the Churchill Hospital.

**Figure 1:** Trial flow chart

[figure not shown]

A summary timeline of the trial is shown on figure 1 above. For participants with T1D, the trial is divided into 5 steps, and involves 5 hyperinsulinaemic hypoglycaemic clamps. Once step 1 (no medication) has been completed, the participants with T1D will be randomised to a sequence of glibenclamide doses for the subsequent steps, followed by a single dose of 10mg dapagliflozin. There will be a washout phase of at least 48 hours between each step (the half-life of the glibenclamide suspension is 8 hours) [1]. Participants without diabetes will undergo a single hyperinsulinaemic hypoglycaemic clamp, as they will not receive any study medication.

The total daily dose as defined by the dosing schedule will be split into AM and PM as shown in

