**Table 2.**

**Table 2 : Oral glibenclamide suspension doses and volumes**

| Total dose | Strength | AM     | PM            | Total volume over 14 days (min) | Total volume over 18 days (max) |
|------------|----------|--------|---------------|---------------------------------|---------------------------------|
| 0.3mg      | 0.6mg/ml | 0.25ml | 0.25ml        | 7ml                             | 9ml                             |
| 0.6mg      | 0.6mg/ml | 0.5ml  | 0.5ml         | 14ml                            | 18ml                            |
| 3mg        | 0.6mg/ml | 2.5ml  | 2.5ml         | 70ml                            | 90ml                            |
|            |          |        | Total: | 91ml                     | 117ml                    |

As mentioned above, for participants with T1D the final hyperinsulinaemic hypoglycaemic clamp will involve them taking a single dose of dapagliflozin 10mg orally at the start of the study visit.

The main pharmacologically relevant site of action of dapagliflozin (Forxiga, AstraZeneca), is the sodium-glucose cotransporter 2 in the proximal convoluted tubules of the kidneys. By inhibiting this transporter, the threshold for glucose reabsorption is reduced, leading to increased glucose excretion.

Dapagliflozin also leads to increased plasma glucagon secretion by acting directly on the pancreatic islet cells [2]. Plasma glucagon concentrations are increased compared to baseline 2 hour after dapagliflozin administration, and reach a peak of 79pg/ml (23.7pmol/L) after 4 hours [3].

In total there will be 8 study visits for participants with T1D and 1 study visit for the non-DM participants.

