## **5 Statistical Methodology**

The statistical methodology for the main primary analysis is described below. Analyses will use the ITT population (section 3.2) for primary and exploratory endpoint(s), and safety population for safety endpoint(s). All statistical significance will be assessed using

an alpha value of 0.05 (95% confidence interval). The summary statistics and statistical estimates will be presented with one decimal place unless more decimal places are needed to interpret the data. All p-values will be rounded to 3 decimal places. All Tables and Figures documented in this SAP are shell versions of the anticipated results and output formats of the analyses to be conducted for the study.

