#### **5.4.4 Safety Analysis**

1. To measure the frequency of adverse events in participants treated with Glibenclamide and Dapagliflozin at each study visit.

Descriptive statistics in form of percentages will be used to determine the proportion of adverse events.

Summary tables for adverse events will include the following:

- Counts (percentage) of subjects with any AEs by treatment and sequence.
- Counts (percentage) with any TEAEs by treatment and sequence.
- Counts (percentage) of subjects with any related TEAEs (AR) by treatment and sequence
- Counts (percentage) of subjects with any serious TEAEs (SAE) by treatment and sequence
- Counts (percentage) of subjects with any related serious TEAEs (SAR) by treatment and sequence

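### As worded, the safety population requires both drugs, so a participant who takes glibenclamide but leaves before the final dapagliflozin visit drops out of every adverse-event table; the set named for the control comparisons also omits the controls

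*SAP*

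**What the plan says.** **Safety set.** SAP section 3.4 defines it as "the set of all randomised patients who were treated with glibenclamide and dapagliflozin". Section 5 assigns the analysis sets: "Analyses will use the ITT population (section 3.2) for primary and exploratory endpoint(s), and safety population for safety endpoint(s". Section 3.5 plans no other population. Section 5.4.4 lists the tables built on the safety set, beginning with "Counts (percentage) of subjects with any AEs by treatment and sequence" and going on to treatment-emergent, related, serious and related serious events.

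**Order of treatment.** The Introduction describes glibenclamide given "orally for a maximum of 54 days (at 3 different doses, in 3 blocks of 14-18 days), followed by a single oral dose of dapagliflozin". The text below Table 2 in section 1.2 confirms the timing of the second drug: "the final hyperinsulinaemic hypoglycaemic clamp will involve them taking a single dose of dapagliflozin 10mg orally at the start of the study visit".

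**Set for exploratory endpoints.** Section 3.2 states: "The intention to treat population (ITT) is defined as the set of all randomised patients". Section 1.2 says who is randomised: after the unmedicated first step, "the participants with T1D will be randomised to a sequence of glibenclamide doses for the subsequent steps". For the control group it says: "Participants without diabetes will undergo a single hyperinsulinaemic hypoglycaemic clamp, as they will not receive any study medication".

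**The concern.** A safety population is normally defined by exposure, so that everyone who took study drug is counted. Here membership depends on having received the last drug in a fixed order. The people left out are those who stopped during glibenclamide, and some of them may have stopped because of an adverse event. In a group of 20, one such omission can change what is reported about serious events.

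The second issue concerns the controls. They are never randomised, yet the set named for the exploratory endpoints contains only randomised patients. An analyst who applies sections 3.2 and 5 to the letter cannot run the comparisons that section 5.4.1 specifies.

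**Working it through.** **1. Who is in the safety set under the literal rule**

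| Participant | Glibenclamide | Dapagliflozin | In set (section 3.4) |
|---|---|---|---|
| Leaves after baseline clamp, before any drug | no | no | no (no on-treatment events to lose) |
| Leaves during or after a glibenclamide block, before the last clamp | yes | no | **no** |
| Reaches the last clamp and is dosed | yes | yes | yes |

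The middle row is the defect. The SAP expects such people. Section 1.3.4 allows 5% dropout, section 5.1 describes discontinuation by treatment and period, and section 2.1.4 withdraws a participant who has two or more missing post-baseline primary values.

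**2. Size**

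Inputs: n = 20 participants with type 1 diabetes and dropout p = 0.05, both from section 1.3.4. The SAP gives neither the timing of dropout nor the reasons. The calculation assumes that every dropout occurs after the first glibenclamide dose and before dapagliflozin, and that participants drop out independently.

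- Expected number removed: n × p = 20 × 0.05 = 1.
- P(at least one removed) = 1 − (1 − p)^n = 1 − 0.95^20 = 0.642.
- P(at least two removed), same binomial = 0.264.

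These are upper bounds at the 5% rate. If, as an assumption, only half of the dropout falls in that window, p becomes 0.025. The expected number is then 20 × 0.025 = 0.5, and the probability of at least one is 1 − 0.975^20 = 0.40.

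**3. Effect on a reported rate (hypothetical cases)**

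- The one leaver had the only serious event: true 1/20 = 5.0%, reported 0/19 = 0%.
- The one leaver had no event and a completer had the only one: true 1/20 = 5.0%, reported 1/19 = 5.3%.

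The direction of the error therefore depends on why people leave. It is downward when leaving is related to adverse events.

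**4. Controls and the randomised-only set**

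- Section 3.2: the set is all randomised patients.
- Section 1.2: only participants with type 1 diabetes are randomised; the controls have one clamp and no drug. So 0 of the 10 controls are in the set.
- Section 5: this set is used for the exploratory endpoints.
- Section 5.4.1: items 1, 2, 4, 5 and 6 of seven compare with the non-diabetic group. Items 3 and 7 are restricted to type 1 diabetes.
- Table 3: four of the listed comparisons are against the non-diabetic group.

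The named set and the specified comparisons cannot both be followed. The primary endpoint (sections 2.1.1 and 5.3.1) is restricted to type 1 diabetes and is not touched.

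**The case against.** **The word 'and' may have meant either drug.** Sections 1.1.3, 2.2.2 and 5.4.4 pair the two drugs with the same word when they name the treatments under study, and section 5.4.4 counts events by treatment and at each visit. That intention is plausible. In section 3.4, however, the phrase is the membership rule that will be programmed, and nothing in the SAP says that one drug is enough. The objection bears on intent; the wording still has to change.

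**Reading too much into the numbers.** A reader might take 64% as the likely chance of losing someone, or conclude that adverse-event rates will certainly be too low. The SAP supports neither. It gives no timing for dropout, and people withdrawn for missing glucagon values need not have had an event. Nor is the stopping rule in section 2.1.3 affected, since it counts participants and not members of the safety population.

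**Reading too much into the control issue.** A reader might infer that the comparisons would be run without controls. Section 5.4.1, Table 3 and the non-diabetic column of Table 5 make it clear that the controls are meant to be analysed. What stands is a set definition that contradicts those instructions.

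**Layout of the adverse-event tables.** A reader might also object to setting percentages from blocks of 14-18 days beside those from a single dose, or to the split by sequence. The tables are descriptive and no between-drug test of event rates is planned. The observation window after dapagliflozin is not given in this SAP, so time at risk cannot be compared. Those are reporting preferences and not errors.

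**Conclusion.** Section 3.4 is wrong as written. Followed literally, it removes from every safety table any participant who took glibenclamide but did not reach the dapagliflozin visit, and section 3.5 leaves no fallback. At 5% dropout the loss is up to 1 of 20 expected, with a probability of up to 0.64 of losing at least one. Both figures rest on all dropout falling between the two drugs. Rates are biased downward if leaving is related to adverse events.

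The mismatch between the randomised-only set and the control comparisons is a real but secondary inconsistency. It affects the set named for five of seven exploratory analyses and all 10 controls. Neither defect alters the primary analysis.

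**What to change.** 1. **Section 3.4:** define the safety population as all participants with type 1 diabetes who received at least one dose of glibenclamide or dapagliflozin. Attribute each adverse event to the treatment at onset, and state how an event that begins in a washout is assigned. Under this definition no treated participant is lost.
2. **Sections 3.2, 3.5 and 5:** add an analysis set for the control comparisons, made up of all randomised participants with type 1 diabetes plus all non-diabetic participants who had a clamp. Name it for exploratory analyses 1, 2, 4, 5 and 6. Keep the present set for the primary analysis.

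The cost is SAP wording and table denominators. The change requires no new data and no change to conduct, and the Introduction already provides for amending the SAP when planned analyses change. It should be made before database lock.
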